### Baseline and follow-up visit**s**

A flow diagram of enrollment, interventions, and assessments for participants (participants timeline) is presented in Table 2.

**Table 2 Tab2:**
[figure not shown]
A flow diagram of enrollment, interventions, and assessments for participants

*Abbreviations*: *t1*, 1–6w (concurrent chemoradiotherapy); *t2*, 11–14w; *t3*, 15–18w; *t4*, 19–22w; *t5*, 23–26w; *t6*, 27–30w; *t7*, 31–34w (6 cycles of adjuvant treatment); *CBC*, complete blood counts; *KPS*, Karnofsky Performance Score; *MRI*, magnetic resonance imaging

#### Baseline evaluation: conducted within 2 weeks before the start of the trial

Demographic dataPast medical history (diagnosis and treatment)KPSHead MRIThe molecular prognostic markers: IDH status (IDH-wildtype/IDH-mutant) and MGMTp status (unmethylated/methylated)Laboratory test: complete blood counts (CBC) and liver and renal function

#### During intervention

Laboratory test: complete blood counts (CBC) and liver and renal function (monitored weekly)KPS (every 3 months)Head MRI (every 3 months)Objective response rates (every 3 months)Adverse events and concomitant medications

#### Follow-up: every 3 months after treatment

KPSHead MRIObjective response ratesAdverse eventsSurvival statusAny new anticancer treatment(s)

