**Methods/design:**

This is a double-blind and randomized clinical trial conducted in a single center. One hundred forty-two patients will be recruited and screened for the inclusion and exclusion criteria. Then, eligible participants will be randomly assigned to an experimental group or a control group in a 1:1 ratio. Based on the administration of radiation therapy (RT), participants in the experimental group will be prescribed levetiracetam plus temozolomide chemotherapy for 34 weeks while participants in the control group will receive placebo tablets plus temozolomide for the same duration. A 3-year follow-up will be conducted on all patients after intervention. Accordingly, the primary outcome will be progression-free survival (PFS). The secondary endpoints include overall survival (OS), the Karnofsky Performance Status (KPS), the objective response rate (ORR), and adverse event incidence.

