## Methods/design

### Study design

This is a prospective, single-center, randomized, double-blind, clinical trial to be conducted at the Second Affiliated Hospital of Chongqing Medical University in China. The study was registered with the Chinese Clinical Trial Registry on 14 August 2021 (ChiCTR-2100049941). The plan is to recruit 142 eligible subjects and assign them to either the control group (standard TMZ chemoradiotherapy) or the experimental group (TMZ plus LEV chemoradiotherapy) at a 1:1 ratio. Participants will undergo a 34-week treatment period and a 3-year follow-up period. The trial flow chart is shown in Fig. 1. The study protocol rigorously follows the Standard Protocol Items: Recommendations for Interventional Trials 2013 (SPIRIT 2013) checklist (see Additional file 1).

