### Outcomes

2.3.1 Primary outcome

The primary outcome is the PFS of patients, the time from randomization and group allocation to any recorded disease progression, and even death.

2.3.2 Secondary outcomes are as follows:
Overall survival (OS), the time from randomization and allocation to death for any reasonThe Karnofsky Performance status scale (KPS). The scale measures the levels of patient activity and medical needs. The score ranges from 100 (no signs of disease) to 0 (dead).Objective response rate (ORR) = (CR + PR)**/**total number of cases × 100%. A complete response (CR) is defined as the disappearance of all target lesions. A partial response (PR) is defined as a reduction of at least 30% in the sum of diameters of the target lesions, considering the baseline sum diameters as a reference. The ORR will be determined by MRI according to the Response Evaluation Citeria in Solid Tumors (RECIST) [20].Incidence of adverse events (AEs). Adverse events (CTC-Toxicity ≥ grade III) will be recorded and analyzed based on the Common Terminology Criteria for Adverse Events (CTC-AE) [21].

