#### Safety evaluation

Incidence of adverse events (CTC-Toxicity ≥ grade3) will be expressed as the number of patients (percentage) and be analyzed by the chi-square (*χ*^2^) test.

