### Reports of adverse events

Adverse events (AEs) will be assessed primarily by abnormal variations in laboratory data (including complete blood counts (CBC), liver function tests (total bilirubin level, AST, ALT), renal function tests (creatinine clearance, blood urea nitrogen), and clinical symptoms. The occurrence, severity level, management strategies, the causality related to the experimental agents, and the termination of all adverse events (AEs) will be recorded and preserved during clinical trials and follow-up. All severe adverse events (CTC-Toxicity ≥ grade3) will be reported promptly to the principal investigator and the research ethics committee (REC). The researchers and clinical trial institutions will ensure that the subjects are treated appropriately and informed truthfully of the relevant information. According to China’s Code of Quality Management for Drug Clinical Trials, researchers are responsible for the cost of dealing with adverse reactions and compensation for patients who suffer adverse reactions. Participants are not provided with specific post-trial care.

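### Grade 3+ adverse events are recorded through treatment plus 3 years of follow-up but compared as a crude percentage of patients, so a survival difference alone can produce an apparent toxicity difference

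*Protocol article*

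**What the plan says.** **Observation period.** The Study design section states: "Participants will undergo a 34-week treatment period and a 3-year follow-up period". The Abstract applies the follow-up to everyone: "A 3-year follow-up will be conducted on all patients after intervention".

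**What is collected after treatment.** The list for the three-monthly follow-up visits reads "KPSHead MRIObjective response ratesAdverse eventsSurvival statusAny new anticancer treatment(s"); its items run together in the text at hand. Response, adverse events and new anticancer treatment are thus recorded at the same visits.

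**Adverse events.** Under Reports of adverse events, all events "will be recorded and preserved during clinical trials and follow-up", and the record includes "the causality related to the experimental agents". The analysis is given under Safety evaluation: "Incidence of adverse events (CTC-Toxicity ≥ grade3) will be expressed as the number of patients (percentage"), tested by chi-square. That section does not limit the count to a period or to treatment-related events, and it does not divide by time observed.

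**Response.** The secondary outcomes define "Objective response rate (ORR) = (CR + PR") over the total number of cases. Partial response is measured against the baseline sum of diameters, using RECIST. No cut-off at progression or at new anticancer treatment is stated.

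**The concern.** A percentage of patients with at least one event treats every patient as if observed for the same time. Here observation can run for more than three years after the last study dose and ends early mainly through death. If levetiracetam prolongs survival as the design assumes, its arm is watched for longer and collects more patients with a grade 3+ event, even if the drug adds no toxicity. Events of later therapy or of recurrence would also enter the count. The safety comparison would then be hardest to read in the case where the trial succeeds, because longer survival could pass for toxicity.

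The response rate has a related but weaker gap: nothing in its definition excludes a response to a later treatment.

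**Working it through.** **The plan's own figure.** The article gives no figure for adverse events or response. Its only calculated figure is the sample size of 142, which uses overall survival medians of 14.6 and 24 months. To see whether those medians with exponential survival fit the stated design:
- Hazard ratio 14.6/24 = 0.608. Freedman's formula, one-sided 0.05, 80% power, gives 105 events.
- With 3 years of uniform accrual and 3 years of further follow-up, the mean event probability is 0.8467.
- 105/0.8467 = 124.01, rounded up to 125; 125/0.9 = 139, within 3% of 142.

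The medians can therefore be used as the design's own survival assumption.

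**Inputs**
- Treatment t = 34/52 × 12 = 7.85 months; follow-up 36 months; total T = 43.85 months (Study design).
- Death hazards λ = ln 2/median: 0.04748 per month on control, 0.02888 on levetiracetam (Sample size).
- Monthly hazard a of a first grade 3+ event, equal in both arms. The article gives none, so a = 0.01 to 0.05 is an **assumption**.
- Observation is taken to end only at death or at T; dropout is ignored.

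**Step 1: time observed.** Mean = (1 − e^(−λT))/λ.
- Control: (1 − 0.1247)/0.04748 = 18.4 months.
- Levetiracetam: (1 − 0.2819)/0.02888 = 24.9 months, a ratio of 1.35.
- Over the 34 treatment weeks alone: 6.6 and 7.0 months, a ratio of 1.07.

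**Step 2: patients with an event before death.** P = a/(a + λ) × [1 − e^(−(a+λ)W)], where W is the counting window.

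| a per month | W = 43.85 months: control | levetiracetam | gap (points) | W = 34 weeks + 1 month: gap (points) |
|---|---|---|---|---|
| 0.01 | 16.0% | 21.0% | 5.0 | 0.6 |
| 0.02 | 28.1% | 36.1% | 8.0 | 1.0 |
| 0.03 | 37.4% | 47.1% | 9.7 | 1.5 |
| 0.05 | 50.6% | 61.4% | 10.8 | 2.2 |

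The true effect on toxicity is nil in every row.

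**Step 3: different hazards on and after treatment.** Let a apply for t months and b for the next 36: P = P(a, t) + e^(−(a+λ)t) × P(b, 36).
- With a = 0.03 to 0.05 and b = 0.01 to 0.06 (assumed), the full-period gap is 5 to 12 points. With 71 per arm, the nominal 5% chi-square test rejects in about 10% to 31% of trials.
- Counting only the 34 weeks, the gap is 1 to 2 points and rejection 5.4% to 5.7%.
- With a = 0.05 and b = 0.005, the full-period gap is 3.7 points, of which 1.8 already arise on treatment.
- With equal survival the gap is zero for any a, b and W.

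**Step 4: exposure adjustment.** Under a constant hazard, mean time to first event, death or the end of W is [1 − e^(−(a+λ)W)]/(a + λ). Dividing P by it returns a in both arms, so a rate per patient-month does not show the gap.

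**Response.** The article gives no response or salvage rates, so no figure can be computed.

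**The case against.** **Collection is not analysis.** The follow-up list is a visit checklist, and the reporting section says what is recorded. Neither says that events or responses after new anticancer treatment enter the comparison, and counting windows are often left to an analysis plan, which is not shown here. This stands in part. For adverse events, however, the article fixes the recording period, the summary measure and the test, and a plan that follows them inherits the problem.

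**Causality is recorded.** True, but the Safety evaluation section does not restrict the count to related events. The causality and new-treatment records make a restricted analysis possible; they do not specify one.

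**The size is assumed.** This stands. Every event hazard is an assumption, and a low post-treatment hazard shrinks the gap. The follow-up is 36/43.85 = 82% of calendar time, but because of deaths only about 64% (control) and 72% (levetiracetam) of the time patients are actually observed. Earlier salvage therapy on control could also add events there and offset the gap. The calculation covers survival only, so the net direction is not established.

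**Full follow-up is a legitimate choice.** Counting all events under intention to treat captures late toxicity, and longer survival would itself be an effect of randomised treatment. That supports reporting late events, but not testing a crude percentage over unequal observation times.

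**Response.** A reader might infer that responses to salvage therapy bias the response rate in a known direction. The article does not support this. Such a response counts only if lesions fall at least 30% below baseline, and whether the cited response criteria supply a best-response rule cannot be checked from the article.

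**Conclusion.** The concern holds for adverse events, as a condition and not as a prediction. If all recorded grade 3+ events are compared as the Safety evaluation section describes, and survival differs as the sample size section assumes, the levetiracetam arm would show about 5 to 11 points more patients with an event without added toxicity. Over treatment plus 30 days the figure is about 0.6 to 2.2 points. This rests on exponential survival, an equal and constant event hazard of 0.01 to 0.05 per month, no dropout, and survivors completing the 34 weeks. The gap shrinks with a low post-treatment hazard and is zero with equal survival.

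A reader might go further and conclude that salvage therapy and unequal survival, not levetiracetam, will determine both comparisons. The article does not show that: it does not state that post-salvage data are counted, the effect needs a survival difference, and even the least favourable case examined gives about 31% rejection.

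The response point is secondary and unquantified: its definition should name a cut-off. No corresponding problem is shown for the performance status scale. Both affected outcomes are secondary, and progression-free survival is untouched.

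**What to change.** **Safety evaluation section:** base the between-arm comparison on grade 3+ events from first dose to a fixed window after the last study dose, for example 30 days. Present later events, including those after new anticancer treatment, separately by arm or as rates per patient-time.

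**Secondary outcomes, objective response rate:** define it as best response before progression or new anticancer treatment, whichever comes first.

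**Cost:** wording only, and best settled before unblinding. The article already provides for recording medications, dose changes and new anticancer treatments; the sponsor should confirm that their dates are captured. The downside is that late events leave the headline test and appear only in the separate presentation. A small residual imbalance also remains, because patients who die or stop treatment early have a shorter window.

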### Sample size

The determination of sample size was calculated by PASS 15.0 software. Based on a previous study and clinical assumptions [26], the median OS of standard care for GBM is 14.6 months while that of the experimental group (TMZ plus LEV ) is 24 months. Statistical parameters are set as follows: one-sided log-rank testing with 80% power, the probability of obtaining a false positive with a statistical test at 0.05, and a 3-year follow-up time. Considering a potential dropout rate of 10% across both groups, it is estimated that 142 patients will need to be enrolled (71 participants per group).

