Studies have demonstrated that the combination of LEV and TMZ is emerging as an optimal approach for improving the survival of GBM patients after surgery. It is therefore essential to conduct a prospective randomized controlled trial (RCT) to evaluate the effectiveness of TMZ plus LEV compared with TMZ standard chemotherapy. Seventy-three patients were enrolled in a Korean study (NCT02815410) that evaluated the effectiveness of LEV in GBM treatment. No differences were found in survival as a result of LEV. LEV had no significant side effects or overdose symptoms in the study, even when patients received an increased dose of up to 2000 mg/day and other AEDs as well [19]. However, the study was limited by a single-arm study design with external and historical control. In China, there is no correlative, randomized, and controlled trial that has been conducted to investigate the effects of LEV for GBM. As a result, we decided to conduct an RCT to explore the therapeutic effect of LEV plus TMZ for GBM, and thus provide an available therapeutic option for the treatment of GBM. The primary objective of this RCT is to determine whether the combination of TMZ and LEV is superior to standard TMZ chemotherapy in prolonging the progression-free survival (PFS) of GBM patients after surgery. This trial will also evaluate the efficacy of new chemotherapy regimens in improving the overall survival (OS), objective response rate (ORR), and the Karnofsky Performance status scale (KPS).

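### The 142 patients and 80% power are calculated for overall survival, but the primary endpoint is progression-free survival, so the primary test has no stated power

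*Protocol article*

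**What the plan says.** The protocol article is consistent about which endpoint is primary. The Background states the primary objective as whether the combination "is superior to standard TMZ chemotherapy in prolonging the progression-free survival (PFS) of GBM patients after surgery". Under Outcomes it says: "The primary outcome is the PFS of patients, the time from randomization and group allocation to any recorded disease progression, and even death". The Discussion again names PFS as the primary outcome indicator. The Abstract lists OS among the secondary outcomes: "The secondary endpoints include overall survival (OS), the Karnofsky Performance Status (KPS), the objective response rate (ORR), and adverse event incidence".

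The Sample size section uses a different endpoint. Its only effect assumption is that "the median OS of standard care for GBM is 14.6 months while that of the experimental group" is 24 months. The other parameters are "one-sided log-rank testing with 80% power", a false-positive probability of 0.05, 3 years of follow-up and 10% dropout. They lead to 142 patients, 71 per group. No section gives a PFS assumption or explains why a size chosen for OS should serve PFS.

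**The concern.** A sample size calculation should show that the primary hypothesis can be tested with adequate power. Here the only calculation concerns a secondary endpoint. The section labels its medians correctly as OS, but its 80% is the only power figure in the article, so readers are likely to attach it to the primary result.

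The main risk is in reading a null PFS result. Whether it is evidence against a worthwhile effect, or merely inconclusive, depends on the PFS effect the trial could detect, and the article does not give one. Power for PFS equals or exceeds the stated figure only if the PFS HR is about as strong as the assumed OS HR. The article neither claims nor supports that.

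**Working it through.** **1. Is the input really OS?** Yes. The Discussion gives 14.6 months as the median survival with temozolomide in the cited trial, against 12.1 months in the comparison arm. It is not a PFS median with the wrong label.

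**2. Do the OS inputs lead to 142?** Inputs from the Sample size section: medians 14.6 and 24 months, one-sided 0.05 (z = 1.645), 80% power (z = 0.842), 36 months of follow-up, 10% dropout. From Recruitment and eligibility criteria: 36 months of accrual. Exponential survival and uniform accrual are assumed.

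- HR = 14.6/24 = 0.608; ln HR = −0.497.
- Schoenfeld deaths = 4(1.645 + 0.842)²/0.497² ≈ 100.
- Freedman deaths = [(1 + 0.608)/(1 − 0.608)]² × (1.645 + 0.842)² ≈ 104.3, rounded up to 105.
- Probability of death with 36 + 36 months: 0.913 (control) and 0.780 (experimental), mean 0.847.
- Freedman size: 105/0.847 ≈ 124, or 126 when each arm is rounded up to 63. Dividing by 0.9 gives 140, against 142 stated.

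The Schoenfeld version gives 134. If every patient has exactly 36 months of follow-up, the result is 154 (Schoenfeld) to 160 (Freedman). A two-sided test with 36 + 36 months gives 169 to 176. The closest match is thus the one-sided OS calculation with 36 + 36 months. On any reading of the follow-up the calculation is for OS.

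**3. What would the same patients give for PFS?** The article supplies no PFS input, so these are assumptions: control median PFS 5 to 12 months, exponential PFS, 36 + 36 months, and 128 evaluable patients (142 × 0.9 = 127.8).

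- Expected PFS events = 128 × mean event probability ≈ 114 to 128.
- One-sided power = Φ(½√d × |ln HR| − 1.645), where d is the number of events.
- Events needed for 80% power = 4(1.645 + 0.842)²/(ln HR)².

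| Assumed PFS HR | One-sided power, 128 evaluable | PFS events needed for 80% |
|---|---|---|
| 0.608 (OS value carried over) | 84–88% | about 100 |
| 0.70 | 61–64% | about 195 |
| 0.75 | 47–49% | about 299 |

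The PFS HR detectable with 80% power is exp(−2(1.645 + 0.842)/√d): 0.63 at 114 events and 0.64 at 128. The control median hardly moves these results; the assumed PFS HR does. From an HR of 0.70 upwards, the events needed exceed all 142 patients.

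**The case against.** The strongest objection is that sizing on OS is conservative for PFS. PFS counts progression or death, so under the same follow-up there cannot be fewer PFS events than deaths. The expected 114 to 128 events exceed the roughly 100 to 105 deaths the OS calculation needs, and at an HR of 0.608 the PFS power is above 80%. This stands, and it means the mismatch does not prove the trial underpowered. It settles only the number of events. The HR is the other half of the calculation, and the article gives none for PFS. The Background also reports that an earlier prospective single-arm study found no survival difference with levetiracetam.

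Two further points have some force. The HRs of 0.70 and 0.75 are scenario values, not properties of this trial; they show sensitivity and no more. And dropping 10% of patients outright is pessimistic under an intention-to-treat log-rank analysis, where those who leave contribute until censoring. With all 142 counted and the same assumptions, one-sided power is about 88–90% at 0.608 and 65–68% at 0.70. The truth lies between the two sets of figures, and the conclusion does not change.

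It could also be said that a journal article leaves detail to a fuller document. That does not apply here: the article presents a whole calculation, and it is for an endpoint other than the one it calls primary.

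**Conclusion.** The concern holds. The 142 patients and the 80% power belong to OS, a secondary endpoint, and the article states no power for its primary PFS test. The textual mismatch rests on no assumption.

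Its consequence cannot be fixed at one number from this document. Under the assumptions above, power for PFS may be a little above the stated 80% or well below it, and the dividing line is a PFS HR of about 0.63–0.64. This must be corrected, because the only power figure given does not refer to the primary hypothesis.

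**What to change.** Rewrite the Sample size section around PFS. State the control median PFS and its source, the target PFS HR, the number of PFS events required, and the power that 142 patients give. If no PFS effect can be justified, report instead the PFS HR detectable with 80% power at the planned size. Keep the 14.6 versus 24 month calculation, labelled as the power for OS as a secondary endpoint.

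Trial status says patients are already being recruited, so the revised section should be dated and should say that the PFS assumptions were set after recruitment began and without sight of outcome data by group, if that is so.

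The cost is one rewritten section and a rerun of the software. Restating power for the fixed 142 requires no extra patients, though the figure may be less favourable than 80%. If the sponsor instead wants 80% power for a PFS HR of 0.70 or weaker, 142 patients cannot supply the events, and the article should say so.

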### Randomization and blinding

Eligible subjects will be randomly divided into two parallel pairs of groups in a 1:1 ratio according to a software-generated random sequence (produced using SPSS software). Before study group assignment, the allocation sequence will be concealed using sealed, opaque, and stapled envelopes that will not be opened by participants or recruiters. The implementation of sequence generation and allocation concealment will be implemented by a researcher who will not be involved in the recruitment process. A specific investigator will be responsible for processing study group assignments.

The participants and outcome assessors will remain blind to the group allocation until the end of the trial. The study data statistician will be unaware of allocations and will not participate in the follow-up visit. Regular unblinding will be performed by the principal investigator and statistical experts for the first time to conduct statistical analysis according to the statistical plan. Researchers will perform a second blinding process to determine which of the two groups is the experimental group. To prevent unnecessary unblinding or harm, the emergency unblinding of allocation will be performed if patients meet the following criteria: (1) severe violation of the treatment plan, (2) severe adverse events during the intervention, (3) patients or their family members request to stop the trial, and (4) visitors who are lost in follow-up.

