### Data collection and management

A case report form (CRF) will be filled in for each participant before intervention. The collection of baseline data, along with primary and secondary outcomes, will be recorded completely in CRF. Each participant (corresponding to a CRF) will be assigned a specific number by which intervention and follow-up will be performed. Using ResMan, an Internet-based Electronic Data Capture (EDC) tool, all information will be kept independently as double copies in a computer. The data files will be locked after a blind audit and confirmed to be reliable. The CRF shall be owned by the principal investigator and shall not be provided to any third party in any form without the written approval of the principal investigator, who will oversee all of the final trial data. A follow-up registration form will be given to all patients to encourage retention. A researcher will collect the reason for loss, survival condition, and recent outcome assessment for participants who lose from intervention. The original paper files will be kept in the filing cabinet of the sponsoring organization and clinical data will be kept for 5 years.

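### The emergency unblinding rule breaks the code automatically on four triggers, with no test that anyone needs the allocation, and conflicts with the commitment to blinding in the same section

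*Protocol article*

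**What the plan says.** The unblinding rule stands in the protocol article under Randomization and blinding. It opens with its purpose, "To prevent unnecessary unblinding or harm", and then lists four triggers. The operative words and the first trigger are: "the emergency unblinding of allocation will be performed if patients meet the following criteria: (1) severe violation of the treatment plan". The next trigger concerns toxicity and is given without a grade: "2) severe adverse events during the intervention". The remaining two concern patients who leave the trial or cannot be reached: "3) patients or their family members request to stop the trial, and (4) visitors who are lost in follow-up". The wording is mandatory. It names no recipient for the code and asks for no judgement that the allocation matters for the patient's care.

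The same section also commits to the following: "The participants and outcome assessors will remain blind to the group allocation until the end of the trial". It adds that the statistician is unaware of allocations.

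Four other places bear on the rule:

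- Reports of adverse events attaches a grade to the word severe: "All severe adverse events (CTC-Toxicity ≥ grade3) will be reported promptly". The incidence of events at that grade is also a secondary outcome (Outcomes; Safety evaluation).
- Sample size allows for loss: "Considering a potential dropout rate of 10% across both groups".
- Data collection and management continues to gather data after a patient leaves: "A researcher will collect the reason for loss, survival condition, and recent outcome assessment for participants who lose from intervention".
- Statistical analysis makes intention-to-treat the main analysis. The follow-up schedule has MRI, KPS, response and adverse events every 3 months.

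**The concern.** An emergency code break is normally justified by one thing: someone treating the patient needs to know the assignment. Here the code is broken whenever a listed event occurs. A severe violation, a request to stop and a loss to follow-up are not emergencies in themselves. The adverse event trigger, read with the grade given in the reporting section, covers any event of grade 3 or higher during the intervention. That includes laboratory findings and is not limited to suspected levetiracetam toxicity.

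The stake is the primary result. PFS counts any recorded progression, so it depends on people reading and recording scans. KPS and adverse event grading also depend on judgement. A patient unblinded for a grade 3 event during the 34-week treatment period stays in the intention-to-treat analysis, with up to 3 years of assessments to come. If the arms differ in tolerability, the unblinding will also differ by arm. Because grade 3 or higher toxicity is itself an outcome, every patient who reaches that outcome during treatment would meet the trigger.

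**Working it through.** **Step 1. Set the passages side by side.**

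| Statement | Consequence if followed as written |
|---|---|
| Aim of the rule: avoid needless unblinding or harm | The code should be broken only for a reason |
| Four triggers, mandatory wording | The code is broken on the event alone, with no reason required |
| Participants and assessors blind to the end | A code break during treatment must not reach either group |
| No recipient of the code is named | Nothing in the rule ensures that it does not reach them |
| Intention-to-treat analysis, 3-monthly visits, outcome data after leaving the intervention | Some outcomes can be recorded after the code is broken |

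The rule conflicts with its own aim. It meets the blinding commitment only if a safeguard is added that the text does not state.

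**Step 2. The planned total.** The documents give no number of patients expected to be unblinded. Their only related figure is the enrolled total of 142, used below as a multiplier. As a check on it:

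- Inputs (Sample size; Recruitment and eligibility criteria): medians 14.6 and 24 months, one-sided 0.05, 80% power, 3 years' accrual and 3 years' follow-up.
- HR = 14.6/24 = 0.608 under exponential survival.
- Freedman events = (1.645 + 0.842)² × (1.608/0.392)², rounded up to 105.
- Mean event probability with uniform accrual: 0.847. Patients: 105/0.847, rounded up to 125 using the unrounded probability.
- With 10% dropout: 125/0.9 = 139, within 3% of 142.

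Other conventions give other totals. Nothing below depends on which was used.

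**Step 3. What the documents alone support.** Dropout 10% × 142 = 14.2, about 14 patients or 7 per arm. This holds only if every planned dropout is a request to stop or a loss to follow-up.

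**Step 4. Adding the adverse event trigger.** The documents give no rate p of patients with at least one grade 3 or higher event during the intervention. The range 10–50% is an assumption.

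- Independent triggers: 142 × [1 − 0.9 × (1 − p)]
- Full overlap: 142 × max(0.10, p)
- No overlap: 142 × (0.10 + p)

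| Assumed p | Independent | Full overlap | No overlap |
|---|---|---|---|
| 10% | 19%, 27 | 14 | 28 |
| 20% | 28%, 40 | 28 | 43 |
| 30% | 37%, 53 | 43 | 57 |
| 40% | 46%, 65 | 57 | 71 |
| 50% | 55%, 78 | 71 | 85 |

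Severe violations of the treatment plan could add to these counts, but the documents give no rate for them either.

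**The case against.** The strongest reply is that the article never says who receives the code, while it does say that participants, assessors and the statistician stay blind. Read together, the code might go only to a treating physician or the principal investigator, and the mechanics may sit in a full protocol that is not shown. This stands in part. A reader might infer that the rule undoes the double blind, and the documents do not support that, because bias in progression or KPS requires that the allocation reach the people who assess. It does not rescue the rule, however. The defect is a stated mandatory trigger without a need to know, not a missing detail.

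A reader might also infer that a large share of patients would be unblinded. The documents do not support that either. The only share that they give is 10%, and for patients truly lost there is little later assessment to bias. Anything larger rests on the assumed rate in Step 4.

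Three further limits are fair:

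- The triggers are bounded in the text: only severe violations count, and only adverse events during the intervention. The grade 3 reading comes from the reporting section, since the unblinding rule itself gives no grade. It is the natural reading, but not a certain one.
- It would go too far to say that knowing the allocation can never help after a stop request or a severe violation. The blinded agent is an antiepileptic, given to patients who often have seizures. Striking those triggers with nothing in their place could close a route to a code break that is needed.
- One might argue that code breaks expose the blocked sequence at a single centre. No block size is given, sequence generation is separated from recruitment, and nothing shows that recruiters learn broken codes. That argument is not relied on here.

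**Conclusion.** The point holds as a conflict within the protocol and a poorly fixed rule. Following the text breaks the code without any medical need being shown, including for patients who stay under assessment for PFS, KPS and adverse events. This contradicts the rule's own purpose and is not reconciled with the commitment to blinding in the same section.

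The supported size is about 14 of 142 patients, provided that all planned dropouts meet the third or fourth trigger. Beyond that, the size depends on an assumed grade 3 or higher rate of 10–50%: about 27–78 patients with independent triggers, 14–71 with full overlap. The direction and amount of any bias in the hazard ratio cannot be derived from the documents, because they do not say who learns the allocation.

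**What to change.** Reconcile the two statements under Randomization and blinding by amendment:

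1. Replace the four automatic triggers with one condition, whatever the event: a documented need to know the allocation for that patient's care. This keeps the route open after a severe violation, a stop request or an adverse event when the need is real.
2. Release the code only to the physician who needs it.
3. State that outcome assessors and the statistician remain blind after a code break.
4. Keep the unblinded patient in intention-to-treat follow-up on the same visit schedule.
5. Record each code break with its date and reason, and report the numbers by arm.

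The cost is a short amendment, a staff briefing and documentation of each code break. The article reports that recruitment is still under way, so the change can protect patients yet to be enrolled or assessed. Blinding already lost cannot be restored at analysis.
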